## Abstract

**Background:**

The appropriateness of lobectomy for all elderly patients is controversial. Meanwhile, sublobar resection is associated with reduced operative risk, better preservation of pulmonary function, and a better quality of life, constituting a potential alternative to standard lobectomy for elderly patients with early-stage non-small cell lung cancer (NSCLC). To date, no randomized trial comparing sublobar resection and lobectomy focusing on elderly patients has been reported. We hypothesized that for patients at least 70 years old with clinical stage T1N0M0 NSCLC, sublobar resection is non-inferior to lobectomy for 3-year disease-free survival (DFS).

**Methods/design:**

This is a prospective, randomized, controlled multicenter non-inferiority trial with two study arms: sublobar resection and lobectomy groups. Comprehensive geriatric assessments will be acquired for each patient. A total of 339 subjects will be enrolled on the basis of power calculations, and participants followed up every 6 months post-operation for 3 years. In case of relapse, survival follow-up will be continued until 5 years or death. Pulmonary function testing will be performed at 6, 12, and 36 months post-operation. The primary outcome is 3-year DFS; secondary endpoints include peri-operative complications and mortality, hospitalization time, post-operative ventilator time, overall survival, 3-year recurrence rates, post-operative pulmonary function, quality of life, geriatric assessment data, and 4-year mortality index.

**Discussion:**

The present study is the only prospective, multicenter, randomized controlled trial comparing sublobar resection and lobectomy for elderly patients. The therapeutic outcomes of sublobar resection will be evaluated in comparison with lobectomy for elderly patients (≥70 years) with early-stage NSCLC.

**Trial registration number:**

NCT02360761: 01/24/2015 (ClinicalTrials.gov)

## Background

Lung cancer is the most commonly diagnosed malignancy and the most common cause of cancer death worldwide, and non-small cell lung cancer (NSCLC) accounts for 80–85 % of those deaths. According to the International Agency for Research on Cancer, an estimated 1.8 million new lung cancer cases and 1.6 million lung cancer-related deaths occurred in 2012 [1].

Lung cancer incidence increases with age. According to the Surveillance, Epidemiology, and End Results (SEER) database, age-adjusted incidence of NSCLC in populations at least 65 years old was about 20 times higher compared with that of younger groups between 2004 and 2008 [2]. As a result of population aging, the proportion of elderly patients is also rapidly increasing. The median age of NSCLC diagnosis rose from 64 years (1974–1978) to 70 in the late 20th century (1999–2003). Forty-seven percent of NSCLC were diagnosed in patients at least 70 years, and 14 % were above age 80 [3]. In 2005–2009, about 71 % of NSCLC cases were newly diagnosed in patients over 70 years, and more than one third were at least 80 years [4]. Although elderly patients have earlier-stage lung cancer at diagnosis compared with younger patients [5, 6], they themselves are somehow under-represented in studies of treatment for cancer [7].

Surgery is the primary option for treating early-stage NSCLC [8, 9]. The Lung Cancer Study Group (LCSG) demonstrated a threefold increase of local recurrence and a tendency toward decreased survival among patients who underwent sublobar resection, and supported lobectomy as the standard of care for stage I NSCLC [10]. However, the appropriateness of lobectomy for all elderly patients is questionable, given that declined function of organs is an independent determinant of post-operative mortality and morbidity, and shorter life expectancy limits the benefit from curative-intent resection [11, 12].

First, lobectomy has been less employed in many elderly patients facing an opportunity for surgical treatment. Although advanced age by itself is not an absolute contraindication to major thoracic surgery [13] and disease-specific survival of elderly patients can be unrelated to age [14–17], many fewer elderly patients with stage I/II NSCLC receive standard lobectomy than the young counterparts. In the US, Nugent et al. reported a resection rate of 6 % in patients no younger than 80 years, although one third of them presented with early-stage disease (stage I or II); meanwhile, one third of patients below 45 underwent thoracic operation, and only 6 % had stage I or II disease [18]. Similarly, in Europe, Damhuis and Schutte found resection rates of 26 % in lung cancer patients younger than 70 years and merely 14 % in those older than 70 years [19].

Second, advanced age is associated with a substantial increase in morbidity and mortality from lobectomy [12]. It was reported that, for patients at least 80 years old, major complication rate is 30 % and that overall mortality rate (in hospital or within 30 days) was 16 % after lobectomy [20]. A retrospective study from the Mayo Clinic reported morbidity and mortality rates of 48.0 % and 6.3 %, respectively, for patients at least 80 years old who underwent lobectomy for lung cancer [21]. Similar conclusions were reached in a population-based analysis, where peri-operative complication rate exceeded 50 % in elderly patients [22].

Third, for elderly patients with early-stage NSCLC, competing risks of dying from co-morbidities may exceed the risk of cancer-related deaths. Evidence from the SEER database indicated that the 5-year probability of dying from cardiovascular diseases is significantly higher than that of dying from cancer in patients 70 to 79 years old who survived for 7 years and those at least 80 years old who survived for 5 years after lobectomy [23]. Limited life expectancy of the elderly restricts the benefit from radical resection.

Lobectomy is not the only option for elderly patients with early-stage NSCLC. Several retrospective studies supported sublobar resection, including segmentectomy and wedge resection, as a sound alternative for the elderly. A retrospective study from the SEER database analyzing 14,555 patients with NSCLC stage I/II suggested that lobectomy conveys benefits only patients younger than 71 years [24]. Similarly, at Pittsburgh Medical Center, Kilic et al. indicated that segmentectomy is associated with reduced peri-operative complications (29.5 % versus 50 %) in patients over 70 years with stage I NSCLC but that local recurrence and overall survival rates are not significantly different [25]. A retrospective study from Japan found that 5-year survival after sublobar resection is significantly inferior to that after standard lobectomy (64.0 % and 90.9 %, respectively, *P* < 0.0001) in the younger group (median age of 68 versus 64); however, in the elderly (median age of 78 versus 77), no substantial difference was observed (67.6 % and 74.3 %, *P* = 0.92) [26]. These data demonstrated that sublobar resection might achieve equivalent benefits compared with lobectomy for the elderly and that the gap in long-term outcome between sublobar resection and lobectomy might shrink as patient age increases. Additionally, sublobar resection may play a better role in preserving the lung function [27, 28], which is important for patients with small lung cancer, conferring long survival, considering the possibility of further lung resections to treat second primary lung tumors.

In summary, sublobar resection may be an alternative to standard lobectomy for elderly patients with early-stage NSCLC, resulting in less operative risk, better preservation of pulmonary function, and improved quality of life (QoL), without compromising survival. However, trials dedicated to surgical assessments are scarce in elderly patients, who comprise a large percentage of all patients.

This randomized trial is, to the best of our knowledge, the first designed to compare sublobar resection and lobectomy for elderly patients in order to address the following open questions: whether in patients at least 70 years old with clinical stage T1N0M0 NSCLC (1) sublobar resection can achieve similar disease-free survival (DFS) compared with lobectomy, (2) sublobar resection can reduce post-operative mortality and morbidity, and (3) sublobar resection can yield better pulmonary function and QoL.

## Methods

### Trial design

The Surgical Treatment of Elderly Patients with early-stage non-small cell lung cancer (STEPS) study was designed as a prospective, randomized, controlled, multicenter non-inferiority trial with two parallel study arms. The hypothesis was that for patients 70 or over with clinical stage T1M0M0 NSCLC, sublobar resection could achieve non-inferior 3-year DFS.

### Eligibility criteria and patient consent

All consecutive patients referred to the surgical units will be assessed to determine eligibility, by one dedicated team member, according to the inclusion and exclusion criteria described below. Each patient will be introduced to the trial by a research group member and receive an explanation of the study protocol. Specific informed consent regarding participation in the trial, randomization, and explanation of the surgery will be obtained before enrolment.

The study will be carried out in accordance with the Helsinki Declaration. It was approved by the Ethics Committee of Peking University Institutional Review Board on 30 October 2014 prior to registration (reference number IRB00001052-13053).

#### Inclusion criteria

Age of 70 years or olderPre-operation criteria (contrast-enhanced computed tomography (CT) scan)▪ Suspected peripheral NSCLC.▪ Clinical stage IA (i.e., T1 N0 M0: tumor diameter of not more than 3 cm, surrounded by visceral pleura, short axis of lymph node of less than 1 cm or negative lymph nodes on positron emission tomography scan)▪ Maximum diameter of consolidation to maximum tumor diameter ratio (consolidation/tumor ratio, consolidation/tumor ratio) no less than 0.5 in sub-solid lesions.▪ Eligibility for sublobar resection with sufficient margin.Intra-operative criteria▪ Histologically confirmed invasive NSCLC (i.e., NSCLC other than pre-invasive adenocarcinomas defined by the International Association for the Study of Lung Cancer: adenocarcinoma *in situ* and minimal invasive adenocarcinoma) [29].▪ Pathological exclusion of suspected lymph node involvement.▪ Feasibility of sublobar resection in terms of surgical margin requirement.General criteria▪ Signed written informed consent by the patient or his or her entrusted party.▪ Completed 4-year mortality index [30] and comprehensive geriatric assessment (CGA) if necessary.▪ Physiology which can tolerate lobectomy (percentage of forced expiratory volume in 1 second (FEV1%) of at least 50 % and diffusing capacity of the lungs for carbon monoxide (DLCO) of at least 50 % in pulmonary function test).

#### Exclusion criteria

Inability to comply with the study procedure.Thoracic surgery history, except for diagnostic thoracoscopy.Malignant tumor history within the past 5 years, except for the following conditions: cured skin basal cell carcinoma, superficial bladder carcinoma, and uterine cervix cancer *in situ*.Any active systemic diseases, including uncontrolled hypertension; unstable angina pectoris; newly onset of angina pectoris within the past 3 months; congestive heart failure (class II or more of New York Heart Association); myocardial infarction within the last 6 months; or severe disease in need of medication, such as arrhythmia, liver, renal, or metabolic diseases.Uncontrollable infections.Co-existing small-cell lung cancer.Psychiatric diseases.Other circumstances deemed inappropriate for enrollment by the researcher.

### Comprehensive geriatric assessments

For patients 70 or older with suspected clinical stage I NSCLC, baseline data—including Vulnerable Elders Survey (VES-13) scale, 4-year survival index, and QoL questionnaires: Functional Assessment of Cancer Therapy-Lung Cancer (FACT-L) and Lung Cancer Symptom Scale (LCSS)—should first be acquired. It is not necessary to conduct further assessments if the patient has a VES-13 score of less than 3; otherwise, the patient will be regarded as ‘high-risk population’, and a further evaluation named ‘pre-operative assessment of cancer elderly (PACE)’ will be mandatory [31, 32]. PACE provides a description of the general health condition of elderly cancer patients prior to receiving surgery comprising assessment disability, instrumental function, depression and cognitive status (activities of daily living, instrumental activities of daily living, Geriatric Depression Scale, and Mini-Mental State Examination score), and an additional important pre-treatment component concerning the level of fatigue (brief fatigue inventory), performance status, concurrent co-morbidities, and anaesthesiologist evaluation of operative risk (American Society of Anesthesiologists, or ASA). Following baseline data acquisition, the 4-year mortality index is required as one of the stratification factors.

### Definition of endpoints and outcome measures

#### Primary endpoint

DFS at 3 years, defined as the time interval from randomization to the earliest onset of any of the following events at 3 years: tumor recurrence, metastasis, or death caused by any reason.

#### Secondary endpoints

Peri-operative measurements▪ Peri-operative complications and mortality. A peri-operative complication is defined as one occurring after surgery and before discharge or within 30 days post-operatively. Death cases during this period should be recorded as peri-operative deaths.▪ Hospitalization time, defined as the time interval from the day of operation to discharge.Chest tube duration, defined as the time interval from the day of operation to that of chest tube removal.Overall survival at 3 years, defined as the time interval from randomization to death from any cause at 3 years.3-year local recurrence and metastasis rates, defined as the rates of loco-regional recurrence and metastasis, respectively, in 3 years from the day of randomization.6-, 12-, and 36-month post-operative pulmonary function, defined as the pulmonary function 6, 12, and 36 months post-randomization.Proportion of video-assisted thoracoscopic surgery procedure, defined as the proportion of video-assisted thoracoscopic surgery in each group.QoL, defined as the QoL questionnaire survey.Prospective CGA and 4-year mortality index, defined as the CGA by VES-13 scale and PACE (if necessary) and the prognostic evaluation of the elderly by 4-year mortality index, respectively.

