### Randomization

The patients who meet the general and pre-operative criteria will undergo surgery, and intra-operative criteria should be evaluated to exclude pre-invasive adenocarcinoma, lymph node involvement, and inadequate surgical margin before randomization. In this procedure, all pre- and intra-operative suspected lymph nodes are biopsied by frozen section sampling before tumor resection to determine whether the patient can be included and randomly assigned in this trial.

The patients meeting the intra-operative criteria will be included and randomly assigned during surgery. The central randomization system will be used with the dynamic minimization random program software; a random number will be assigned to each patient, and the medical center for the surgery will be informed. The patients will be randomly assigned into sublobar resection or lobectomy group by a central computer and further sub-grouped according to age (≤80 or >80 years), pathological type (adenocarcinoma and other types), tumor size (diameter of ≤2 and >2 cm), and 4-year survival index. Once a random number is assigned to a patient, this specific number cannot be re-assigned another one, even if the patient fails to complete the entire study.

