### Adverse event reporting

A data and safety monitoring committee will monitor patient safety, and all ongoing serious adverse events will be closely followed until stabilization. The complications occurring after operation until discharge, or within 30 days post-operation in discharged patients, are considered post-operative complications; death during the same period is defined as peri-operative death. Post-operative complications are described according to the Common Terminology Criteria for Adverse Events 4.1 published (CTCAE version 4.1) by National Cancer Institute of the US, reported, classified, and recorded into case report form (CRF).

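### Patients are randomised during surgery, but peri-operative complications and deaths are counted only after it, so events during the allocated resection fall outside the safety endpoint

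*Protocol article*

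**What the plan says.** All references are to the Protocol article.

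- **Time of allocation (Randomization):** "The patients meeting the intra-operative criteria will be included and randomly assigned during surgery". Suspected nodes are "biopsied by frozen section sampling before tumor resection to determine whether the patient can be included and randomly assigned in this trial".
- **Safety endpoint (Secondary endpoints):** "A peri-operative complication is defined as one occurring after surgery and before discharge or within 30 days post-operatively". On deaths it adds: "Death cases during this period should be recorded as peri-operative deaths".
- **Safety reporting (Adverse event reporting):** "The complications occurring after operation until discharge, or within 30 days post-operation in discharged patients, are considered post-operative complications", and "death during the same period is defined as peri-operative death".
- **Survival endpoints:** DFS is "defined as the time interval from randomization to the earliest onset of any of the following events at 3 years", and the listed events include death from any cause. Overall survival also starts at randomisation and counts all deaths.
- **Question served (Background, second of three):** whether "sublobar resection can reduce post-operative mortality and morbidity".

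**The concern.** In most surgical trials patients are randomised before the operation, and a window that opens after surgery leaves out the whole procedure in both arms. Here allocation comes part-way through the procedure. What remains of the operation is the allocated resection and, where frozen section calls for it, conversion from sublobar resection to lobectomy. That interval follows randomisation and is where the two treatments differ most directly. Bleeding, vascular injury or a cardiac event during it can be a consequence of the allocated procedure, yet the stated rule does not count it.

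This matters more than it would for a minor secondary endpoint. The Abstract and Background justify sublobar resection by reduced operative risk, and the non-inferiority design accepts some possible loss of DFS in return. The safety comparison supplies the benefit side of that trade. The endpoint is also labelled peri-operative, a term a reader would ordinarily take to include the operation.

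**Working it through.** The article states no figure to reproduce, so the check sets the time origins side by side.

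1. **When risk under the allocated arm begins.** Randomization places it within the operation, after the intra-operative criteria are met. The order is explicit for nodal sampling, which precedes tumour resection and decides whether the patient is randomised. The allocated resection must then follow, because its extent is unknown until allocation.

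2. **When each endpoint starts counting.**

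| Endpoint | Start | Complication between allocation and end of operation | Death in that interval |
|---|---|---|---|
| DFS | Randomisation | Not applicable | Counted |
| Overall survival | Randomisation | Not applicable | Counted |
| Peri-operative complications | After the operation | Not counted | Not applicable |
| Peri-operative mortality | After the operation | Not applicable | Not counted |

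3. **Whether another section closes the gap.** Adverse event reporting uses the same late start for complications and for deaths. It also says that a committee monitors patient safety and that ongoing serious adverse events are followed until they stabilise. Intra-operative events may be seen by that route, but nothing brings them into the endpoint.

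4. **Consequence within one report.** A patient who dies during the allocated resection is a DFS event and an overall-survival event, but is absent from peri-operative mortality. Early deaths by arm could therefore disagree between tables.

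5. **Size.** The article gives no intra-operative complication or death rate, so the number missed cannot be calculated. For scale only: if the 339 patients are split equally, 339 / 2 = 169.5 per arm, and each 1 % of patients with such an event is 0.01 × 169.5 ≈ 1.7 patients per arm. Two things make the true loss smaller than a crude intra-operative rate would suggest. Events before allocation (access, nodal biopsy) do not belong to the comparison. An intra-operative injury that leads to a complication or death after surgery is still counted through that later event.

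6. **End of the window.** Secondary endpoints puts it loosely, but Adverse event reporting settles it: until discharge, or 30 days after the operation in patients already discharged.

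**The case against.** The strongest reply is that the endpoint matches its question. The Background asks about post-operative mortality and morbidity, Adverse event reporting calls the events post-operative, and a post-operative window answers a post-operative question. On this view, adding intra-operative events is a preference for a broader endpoint. A condensed article may also leave the recording of such events to the full protocol or the CRF.

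Part of this stands: the wording of the Background question fits the window. But the endpoint itself is named peri-operative, and the article is not silent on its definition. It states the start point twice, and both times that start is later than the article's own randomisation. With 10 planned centres, some may follow the literal wording and others may include the operation.

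Some stronger readings are tempting, but the document does not support them.

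- A reader might infer that a death on the table after allocation belongs to no endpoint. It does belong: DFS and overall survival both count it.
- A reader might infer that the comparison is biased towards one arm. The direction is unknown. If lobectomy has more events during resection, the rule understates the advantage of sublobar resection; if it has fewer, the rule hides a disadvantage.
- A reader might also criticise the variable end of the window and want a cut at day 30 for everyone. The end is clear enough as stated, and such a cut would remove late in-hospital deaths from peri-operative mortality.

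**Conclusion.** The point holds as a defect of definition in one secondary endpoint. Followed literally, the plan leaves complications between allocation and the end of the operation out of the safety endpoint, and leaves deaths in that interval out of peri-operative mortality though not out of DFS or overall survival. The conclusion rests on the literal start points in two sections and on the stated time of randomisation; it needs no assumed event rate. How many events are affected, and in which direction, cannot be derived from the document. The primary endpoint, the sample size, the type I error rate and the non-inferiority conclusion are untouched. It is worth correcting because the excluded interval is the allocated treatment itself and because reduced operative risk is part of the case for the trial.

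**What to change.** Use one identical definition in Secondary endpoints and in Adverse event reporting, under one label. For example: *a peri-operative complication is one with onset from randomisation, the remainder of the operation included, until discharge or, in a patient already discharged, until 30 days after the operation; a death in the same interval is a peri-operative death.* This moves the start and keeps the stated end. Events before randomisation stay outside the comparison.

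The cost is one definition and a check that the CRF records the time of randomisation and any intra-operative event after it. For patients already enrolled, such events would have to be taken from operative records, by the same rule in both arms. Reported complication rates become slightly higher. When the article was written, enrolment was incomplete and peri-operative data were to be analysed at recruitment completion, so the change could be made before that analysis.
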